## Statistical analyses

In order to evaluate the therapeutic potential of each tDCS intervention in post-stroke motor recovery, we will first asses the data distribution of the Fugl-Meyer Assessment by means of Shapiro–Wilk method. In the case of normal distribution, clinical outcomes will be compared using repeated measures analysis of variance (two-way ANOVA) with “TIME” (baseline, post-tDCS, follow-up) as within-subject factor, and “GROUP” (ipsi-DLPFC, contra-CEREB, ipsi-DLPFC + contra-CEREB, SHAM) as between-subject factor. Post hoc pair-wise comparisons will be performed using a Bonferroni correction for multiple comparisons. In the case of non-normal data distribution, a non-parametric Kruskal–Wallis test will replace repeated measures ANOVA. Linear mixed models and Pearson’s (for normally distributed data) or Spearman's correlation coefficients corrected for multiple comparisons between AX-CPT, visuo-motor adaptation task, and the Fugl-Meyer outcomes will be used to explore behavioral correlation between motor, attentional, and cognitive control domains. All data will be presented as mean ± standard deviation and statistical significance will be set for all tests at *p* ≤ 0.05.

In order to characterize the electrophysiological EEG effects induced by our interventions, we will first explore correlations with behavioral data and biomarkers of recovery. First, power spectral density (PSD) changes for each frequency band will be compared between stimulation groups using two-tailed ANOVA (*P* = 0.05), with “TIME” as the within-subject factor and “GROUP” as the between-subject factor. To correct for multiple comparisons, non-parametric cluster-based permutation statistics with Montecarlo sampling (1000 permutations) will be applied, allowing the examination of global effects across all electrodes while controlling for multiple comparisons at the sensor level, without the need of prior assumptions about effect location. Finally, connectivity (imaginary part of coherence measures) and entropy effects (complexity of temporal dynamics) of the electrophysiological response will be also explored. The same statistical procedure as for PSD exploration applying repeated measures ANOVA with non-parametric cluster-based permutation statistics and MonteCarlo sampling (1000 permutation) will be used, with “TIME” as within factor, and “GROUP” as between factor. Individually averaged connectivity and entropy values (total averages) and individual topographical maps at the electrode level will be examined to detect specific regions sensible to the tDCS intervention.

The individual differences across the study follow-up for the Fugl-Meyer Assessment evaluating upper/lower limb motor recovery,visuo-motor adaptation task outcomes assessing cerebellar contributions to motor learning and the AX-CPT task assessing sustained attention and cognitive control will be correlated (Pearson’s or Spearman correlation coefficients, depending on data normality) with the individuals’ electric fields voxel-by-voxel magnitude (an underneath cut-off of 0.25 V/m in total field strength will be positioned as a threshold in the power to induce neuronal effects). Moreover, the |E| and |nE| extracted values and the total injected current will be also correlated with the same outcome measures. Otherwise, E-field components will be correlated with specific EEG features reaching statistical significance in the power spectrum density ($$\mu {V}^{2}$$), connectivity, and complexity analyses. Finally, multivariate regression models will be computed to explore correlations between electrophysiological responses ($$\mu {V}^{2}$$, imaginary coherence and entropy measures), induced E-field, and behavioral outcomes.

All data will be analyzed according to the intention-to-treat principle. The data of all patients with complete datasets (at W0, W3, and W7 time points ) will be analyzed according to their randomized tDCS group. All available data will be included in the analysis. Missing data will be imputed by means of a constrained longitudinal data analysis (cLDA) which will estimate unconditionally lost data.

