## Study objectives

The main and primary “key” objective pursued in this clinical trial is to (1) identify the clinical potential of the multitarget cortical stimulation by comparing the effect of three tDCS interventions (anterior cerebellar lobe stimulation, dorsolateral prefrontal stimulation and the combination thereof) driving clinical improvements of upper limb motor function in stroke patients, as assessed by the Fugl-Meyer Assessment (FMA). We specifically hypothesize (key hypothesis of the study) that combined stimulation of the former two cerebral sites will enhance clinical recovery compared to sham stimulation and also to the stimulation of either site (anterior cerebellar or dorsolateral prefrontal) in isolation.

The secondary objectives of our clinical trial are: (2) to evaluate the influence of such interventions on specific cognitive and motor processes sensitive to the contribution of the modulated targets, i.e., via an impact on sustained attention and cognitive control (dorsolateral prefrontal tDCS) or motor adaptation skills (anterior cerebellar tDCS); (3) to explore whether clinical improvements are induced by isolated interventions or if their combination can be associated to the normalization of neurophysiological outcome measures (increased local and/or inter-areal synchronization or changes of abnormal neural states, taken as proxies of enduring adaptive plasticity); finally, (4) to identify biomarkers (clinical and cognitive scores, neuroimaging features, and electrophysiological measures and tDCS current distribution modelled parameters) associated to the severity of motor impairments and their improvement following stimulation.

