### Sample size

The current study is designed as a pilot clinical trial aiming to assess the effects of an isolated monofocal (single cortical site stimulation, i.e., either the dorsolateral prefrontal cortex or the anterior cerebellar lobe) or combined multifocal (simultaneous stimulation of the two former sites) multiday tDCS intervention using a high-density array of electrodes. Given the exploratory character of our study, no power analysis to estimate sample size was required by the local IRB committee. Instead, following standardized guidelines for experimental clinical trials, we considered the number of participants included in past similar exploratory tDCS studies warranting sufficient statistical power [35] and ensuring recruitment feasibility, and we concluded the need to include at least *n* = 15 patients in each of our 4 tDCS treatment groups.

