### Randomization and blinding

The study will include *n* = 60 patients with chronic MCA stroke, randomly assigned to one of the 4 experimental groups indicated above (ipsi-DLPFC, contra-CEREB, ipsi-DLPFC + contra-CEREB, or SHAM tDCS). A patient randomization algorithm (*MinimPy* software running in *Python environment*, https://sourceforge.net/projects/minimpy/) counterbalancing groups by sex (Woman/Male), age (− 65 years/ + 65 years) and stroke type (ischemic/hemorrhagic) will ensure equivalence for these three variables across the 4 experimental groups. The biased coin method is an algorithm implementing a biased coin minimization algorithm (base probability: 1, allocation ratio 1:1:1:1) [36] for sequential dynamic allocation, in which each new allocation is influenced by the current state of balance across delivered treatments [37].

An independent co-investigator not involved in the recruitment/enrollment of patients, tDCS application or in clinical evaluation will be in charge of patient randomization and condition/group allocation. The groups of patients associated with the four randomized tDCS conditions will be assigned a letter-coded name (Groups A, B, C, or D) providing no clue with regard to the ultimately delivered tDCS strategy. This same code will be used at all times for patient allocation and only an independent co-investigator in charge of randomization/allocation activities will be able to associate each of the codes (A, B, C, and D) to a specific tDCS condition (aka treatment group). Once a patient will be randomly assigned to a condition/treatment group, its code (A, B, C, or D) will be communicated to a team member in charge of stimulation which will simply deliver it blindly in a non-identifiable manner. To search for the potential influence of placebo or nocebo effects, investigators will debrief at the end of the follow-up, with patients and ask them to guess which stimulation group they believed they had been allocated to (allocation perception).

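### The key hypothesis is three contrasts against the combined arm, but the plan reaches them only through an unordered four-group ANOVA with post hoc Bonferroni pairs, and the stated model leaves out the minimisation factors

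*Protocol article*

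**What the plan says.** - **Hypothesis.** Protocol article, Study objectives, gives as the key hypothesis that "combined stimulation of the former two cerebral sites will enhance clinical recovery compared to sham stimulation and also to the stimulation of either site" in isolation.
- **Primary analysis.** Statistical analyses plans a two-way repeated-measures ANOVA of the Fugl-Meyer score if it is normally distributed. TIME has three levels (baseline, post-tDCS, follow-up). GROUP is one factor with four unordered levels: "ipsi-DLPFC, contra-CEREB, ipsi-DLPFC + contra-CEREB, SHAM) as between-subject factor". Then: "Post hoc pair-wise comparisons will be performed using a Bonferroni correction for multiple comparisons". The number of pairs is not given.
- **Level.** The same section states that "statistical significance will be set for all tests at *p* ≤ 0.05".
- **Allocation.** Randomization and blinding describes minimisation on sex, age (cut at 65) and stroke type with base probability 1, which "will ensure equivalence for these three variables across the 4 experimental groups". The model under Statistical analyses names only TIME and GROUP.
- **Size.** Sample size says that no power analysis was required, but also that "we considered the number of participants included in past similar exploratory tDCS studies warranting sufficient statistical power". It settles on "at least *n* = 15 patients in each of our 4 tDCS treatment groups".

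**The concern.** The hypothesis is a conjunction: combined better than sham, better than DLPFC alone and better than cerebellum alone. A conjunction of this kind, or a prespecified order, can be tested with each contrast at the full 0.05 without inflating the error rate. The plan instead leaves the three contrasts inside a post hoc family and divides alpha across it, with no visit named as the deciding one. With 15 patients per arm, that choice has a visible price in power for the comparison the trial is built around.

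Two smaller matters go with it. Factors that steer allocation would normally also enter the analysis, and here the stated model does not carry them. The wording on statistical power is not backed by any calculation in the article.

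**Working it through.** **Inputs from the article.** 15 per arm, four arms, 60 in total; level 0.05; Bonferroni on pairwise comparisons; three contrasts in the key hypothesis.

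**Assumptions.** The article gives no design difference, SD or dropout rate, so the stated sample size cannot be reproduced. I take two-sided tests, no dropout, and a post-minus-baseline contrast with pooled error on 60 − 4 = 56 df. For scale I use a between-arm difference of 6 FMA-UE points. The article gives 6 points only as a within-patient threshold, so this is an illustration. The SD of change is assumed to lie between 5 and 12 points, that is d = 6/SD from 1.2 down to 0.5.

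**Families.** Four groups give 4 × 3 / 2 = 6 pairs, so 0.05/6 = 0.0083. Three key contrasts give 0.05/3 = 0.0167. A fixed order with sham first, or an all-must-succeed rule, uses 0.05.

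**Power for combined versus sham.** Noncentral t with noncentrality d × √(15/2); at d = 1 this is 2.739. The critical values on 56 df are 2.003 (0.05), 2.468 (0.05/3) and 2.735 (0.05/6).

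| Assumed SD of change | d | 0.05/6 | 0.05/3 | 0.05 |
|---|---|---|---|---|
| 5 | 1.20 | 71% | 79% | 90% |
| 6 | 1.00 | 51% | 61% | 77% |
| 8 | 0.75 | 26% | 35% | 52% |
| 10 | 0.60 | 15% | 21% | 37% |
| 12 | 0.50 | 10% | 15% | 27% |

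Correcting for six pairs rather than three contrasts costs about 5 to 10 percentage points. Against a fixed order it costs about 17 to 26.

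**Joint success on all three contrasts** (simulation, d = 1, only the combined arm effective): about 27% at 0.05/6, 37% at 0.05/3 and 57% with each at 0.05. If each single site has half the combined effect, the figures fall to about 3%, 5% and 13%.

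**Detectable difference at 80% power:** 1.31 SD (0.05/6), 1.21 SD (0.05/3), 1.04 SD (0.05). For 6 points, the SD of change would have to be at most 6/1.31 ≈ 4.6 or 6/1.04 ≈ 5.8 in the first and last case.

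**The omnibus test.** Simulated with the 6-df TIME by GROUP interaction at d = 1: about 82% power if only the combined arm works, and 61 to 63% if each single site has half the effect. Requiring it before the 0.05/6 sham contrast costs a further 1 to 6 points. The loss therefore comes mainly from the multiplicity rule.

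**Minimisation factors.** If they explain a share R² of the variance in FMA-UE change, d becomes d/√(1 − R²) on 53 df. At 0.05/6 and d = 1, power moves from 51% to 53% (R² = 0.05), 56% (0.10) or 63% (0.20). If their effects are constant over time, they cancel in the change contrast: simulation gave an adjusted-to-unadjusted standard error ratio of 1.00, so plain main effects would bring nothing.

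**The case against.** **The other pairs have a purpose.** A reader might infer that alpha is spent on comparisons outside the trial's aims. The article does not support that. Study objectives sets out to compare three interventions, the analysis of clinical outcomes compares active conditions with sham, and the Discussion looks for the most beneficial strategy. All six pairs serve a stated aim. What stands is a question of priority: only three of them make up the key hypothesis.

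**The size of the family is inferred.** Six pairs is the natural reading of the Bonferroni sentence, but it is not written. A correction that also multiplies over visits has no support in the text. If the intended family is the three key contrasts, the remaining loss is only against a fixed order or an all-must-succeed rule.

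**Type I error.** A reader might infer that leaving out the minimisation factors makes the nominal 5% tests run off 5%. That is conditional. Simulated error fell to roughly 4 to 5%, 2.5 to 3.6% and 2 to 3% only when the factors explained 10, 20 or 30% of the variance of the analysed score or of its change. With time-constant effects, the change contrast ran at about 5 to 6% unadjusted. Where there is a departure, it is conservative.

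**Scope and pilot status.** Covariates, deciding visit and family size are often left to an analysis plan, and the article does not say that covariates are excluded. It also discloses the exploratory pilot character. This is fair, and I do not count the missing details as errors. However, the article commits to a model with two named factors and to post hoc corrected pairs, names a key hypothesis and speaks of sufficient power. Those statements can be judged as they stand.

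**Conclusion.** The point holds in this form: the stated analysis does not single out the three contrasts that make up the key hypothesis, and the stated model omits the factors used in allocation.

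At 15 per arm and an assumed d of 1, the all-pairs reading gives 51% power for combined versus sham, against 61% or 77% under the two alternatives, and 27% against 57% for the full hypothesis. The direction of the loss is the same over the whole assumed SD range; the size depends on that SD and on the comparator chosen. The benefit of the covariates is uncertain and may be small.

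Restructuring does not make the trial well powered. Even one contrast at 0.05 needs about 1.04 SD for 80% power, so the sample size is the larger limit, and the phrase on sufficient power is not supported by anything in the article.

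**What to change.** 1. In the primary longitudinal model, name one deciding visit and prespecify combined versus sham, combined versus ipsi-DLPFC and combined versus contra-CEREB at that visit. Test them at two-sided 0.05, in a fixed order or with a rule that all three must succeed. Report the other visit and the other three pairs as secondary, with confidence intervals.
2. Include sex, age group (the 65-year cut) and stroke type so that they act on the analysed contrast, either as factor-by-time terms or in a baseline-adjusted model.
3. In Sample size, replace the claim of sufficient power with the difference detectable at 80% power for 15 per arm: about 1.04 SD of change at 0.05 (1.31 SD if 0.05/6 is kept).

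The cost is wording only. The article reports 11 completers, recruitment planned to the end of 2025 and a blinded analyst, so the change can be fixed before unblinding. The downsides are that three pairs lose confirmatory standing, a few degrees of freedom are spent (three for main effects, more with time interactions), and the power statement becomes less favourable.

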### Outcome measures

In agreement with our objectives, the primary outcome measure (addressing the main and key objective) of our trial will evaluate changes in the Fulg-Meyer Assessment (FMA) for the impaired upper limb. A set of secondary outcome measures recorded prior to and following tDCS treatment (addressing study objectives 2, 3, and 4) will assess respectively: (2.1) Patient’s performance in a series of computer-based behavioral tasks evaluating visuo-motor adaptation (anterior cerebellar lobe contributions) and also sustained attention and cognitive control (prefrontal contributions); (2.2) Changes in resting-state and task-evoked EEG recordings and (2.3) set of clinical scales evaluating global stroke severity, cognitive impairment and their recovery, and correlations with predicted electric field distribution model features and stroke lesion hallmarks revealed by structural MRI neuroimaging. Find below a detailed explanation of the different outcome measures employed in our study.

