#### Fugl-Meyer Assessment (FMA)

Addressing the primary or key goal of our study, the Fugl-Meyer Assessment (FMA) will be used to evaluate upper limb motor improvements. This is a widely employed tool used to assess motor impairment in post-stroke participants and considered one of the most comprehensive and reliable quantitative measures for motor hemiplegic dysfunction [46]. Among the sub-sections of this assessment we will focus on evaluating the upper limb/extremity motor domain (FMA-UE). Even so, the lower limb/extremity section of the assessment (FMA-LE) will be also administrated to evaluate the status and changes in lower limb motor function. The FMA-UE and FMA-LE include a series of items measuring movement, coordination and reflexes, each one scored on a 3-point ordinal scale (0 = cannot perform, 1 = performs partially, 2 = performs fully), with a total score of 0 points equaling absolute hemiplegia, and 100 points signalling sound motor function; of these 100 points, 66 are attributed to the upper extremity (FMA-UE) and 34 to the lower extremity (FMA-LE). For intra-subject pre-post-intervention assessments, an improvement greater than 6 points is usually defined as clinically significant.

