## Data analyses

### Analysis of clinical and cognitive performance outcome measures

Outcomes extracted from computer-based tasks and clinical scores (see the previous section) will be analyzed to explore the differential ability of active tDCS conditions compared to sham stimulation to induce upper limb motor recovery following a stroke. For the clinical tests (FMA, NIHSS, MoCA, and hemispatial neglect tests), mean group scores post vs. pre-tDCS baseline intervention,and during the follow-up assessment, will be compared across experimental groups. Sociodemographic data will also be compared between treatment groups (Group 1: ipsi-DLPFC, Group 2: contra-CEREB, Group 3: ipsi-DLPFC + contra-CEREB, Group 4: SHAM) to identify potential collapse factors.

In order to quantify changes in motor performance with the visuo-motor adaptation task,and assess tDCS effects applied over the cerebellum or the dorsolateral prefrontal areas on upper limb voluntary motion, the following set of measures will be used: (i) the angular trajectory error (“SumErr”; cm) estimating accuracy, consisting of the sum of observed deviations from the ideal linear trajectory at peak tangential velocity (PV)for each trial of the motor adaptation block; (ii) the area under the learning curve (AUC) measuring patients’ adaptation rate,calculated by performing a power fit on the mean learning values of each participant; (iii) the coefficient of variation (CV)measuring the variability of motor performance during the adaptation plateau phase (i.e., when the AUC is stabilized and reaches stable levels) and calculated as the standard deviation (SD) divided by the mean over trials belonging to the plateau phase (AUC/Time-to-target). All these metrics will be represented in ordinal and mean group scores for post vs. pre-tDCS baseline intervention, and for the follow-up milestone and compared across tDCS groups.

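### A normality pre-test on FMA scores can swap the TIME × GROUP ANOVA for a Kruskal–Wallis test, which is not equivalent and is not tied to change from baseline or to a visit

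*Protocol article*

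**What the plan says.** The Statistical analyses section of the protocol article opens with a gate: "we will first asses the data distribution of the Fugl-Meyer Assessment by means of Shapiro–Wilk method". If the scores look normal, the analysis is a two-way repeated-measures ANOVA with TIME (baseline, post-tDCS, follow-up) within subjects and GROUP (four arms) between subjects. For pairwise follow-up, "Post hoc pair-wise comparisons will be performed using a Bonferroni correction for multiple comparisons". If they do not look normal, "In the case of non-normal data distribution, a non-parametric Kruskal–Wallis test will replace repeated measures ANOVA".

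Three other places bear on what enters that test.

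- Outcome measures says the primary measure "will evaluate changes in the Fulg-Meyer Assessment (FMA) for the impaired upper limb".
- The analysis section for clinical and cognitive outcomes says the comparison across groups is of "mean group scores post vs. pre-tDCS baseline intervention", and of the follow-up assessment.
- Study objectives gives the key hypothesis that "combined stimulation of the former two cerebral sites will enhance clinical recovery compared to sham stimulation", and also compared with either site alone.

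None of these links change scores, or a particular visit, to the Kruskal–Wallis branch. Linear mixed models are named in Statistical analyses only for relations between motor, attentional and control measures. The constrained longitudinal analysis (cLDA) is named there only for missing data.

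**The concern.** The key question is whether FMA-UE changes more in one arm than in another. In the planned ANOVA that is the GROUP × TIME term. Kruskal–Wallis compares independent groups on a single value per patient. It has no TIME factor, no interaction and no baseline adjustment, and it gives no effect in FMA points. The article gives no longitudinal or baseline-adjusted fallback for this outcome.

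The trigger is also poorly aimed. The ANOVA needs approximately normal residuals, whereas the gate is worded as a test of the score distribution. FMA-UE is a bounded 0 to 66 sum of 3-point items, and the inclusion criteria set no FMA range. A wide or flat spread of severity could therefore fail the test even when changes within patients are well behaved.

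At stake is the sensitivity of the primary comparison. If the fallback is run on raw scores, differences between patients in severity enter the error term and can hide a clinically relevant gain.

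**Working it through.** **Inputs from the article.** There are 4 arms of at least 15, so 4 × 15 = 60, which matches the stated total. Allocation is 1:1:1:1 and significance is set at 0.05. An improvement greater than 6 points is described as usually regarded as clinically significant. The article states no power, SD or effect size, so there is no power figure to reproduce.

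**Assumptions, not in the article.** Baseline FMA-UE is uniform on 5 to 52. Change has SD 6 and is independent of baseline. The combined arm gains 6 points and the other arms gain 0.

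**Step 1: what each response variable does to the noise.**
- Baseline variance = (52 − 5)² / 12 = 2209 / 12 = 184.1.
- Variance of a raw post score = 184.1 + 6² = 220.1, so SD = 14.8.
- SD of change = 6.
- Standard error of a difference between two arms = SD × √(2/15) = SD × 0.365. This is 5.42 for raw scores and 2.19 for change.
- A 6-point gain is therefore 6 / 5.42 = 1.1 standard errors on raw scores and 6 / 2.19 = 2.7 on change.

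**Step 2: four-group omnibus test, closed-form check.** The arm means are 0, 0, 6, 0, with overall mean 1.5. The sum of squared deviations is 3 × 1.5² + 4.5² = 27. The noncentrality is 15 × 27 / variance = 405 / variance.
- Raw scores: 405 / 220.1 = 1.84, giving F-test power on (3, 56) df of about 17%.
- Change: 405 / 36 = 11.25, giving about 78%.

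**Step 3: simulation under the same assumptions (repeated runs agree).**

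| Analysis | Power |
|---|---|
| Kruskal–Wallis, raw post-tDCS score | about 15% |
| Kruskal–Wallis, change from baseline | about 75% to 77% |
| Baseline-adjusted omnibus F test | about 77% to 80% |

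The like-for-like comparison is between omnibus tests. A single baseline-adjusted combined-versus-sham contrast has about 76% power unadjusted and about 50% with Bonferroni for six pairs.

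**Step 4: sensitivity.** A second set of 18 scenarios assumed gains over sham of 3, 3 and 6 points held to follow-up, between-patient SD 15 or 20, between-visit correlation 0.80, 0.90 or 0.95, and three score shapes. Power ranges were:
- GROUP × TIME F test: 12% to 84%
- Kruskal–Wallis on raw post scores: 7% to 13%
- Kruskal–Wallis on change: 12% to 76%
- Rank ANCOVA: 14% to 69%

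With normal scores, SD 15 and correlation 0.90, change has SD 15 × √(2 × 0.10) = 6.7. The four figures are then 53%, 12%, 47% and 42%.

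**Step 5: how often the fallback is taken.** Shapiro–Wilk on all 60 raw scores rejected at one or more visits in:
- 10% to 15% of runs with normal scores
- 9% to 12% with scores clipped to 0–66 at SD 15
- 51% to 68% with clipped scores at SD 20
- 96% to 99% with flat scores

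With flat baseline scores and normal changes, the residuals of a baseline-adjusted model failed in only about 5% of runs. In that case the gate rejects a model whose assumptions hold.

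**The case against.** The best reply is that the article never says raw scores will be used. The primary outcome is worded as changes in FMA, and the clinical tests are described as post against pre. Kruskal–Wallis on change keeps the baseline and tests the GROUP × TIME question for that pair of visits. On the figures above it loses almost nothing against the adjusted omnibus test. This stands. A reader might infer that the fallback necessarily discards baseline, or that the primary question goes largely untested; the documents do not support either. What remains is that the rule itself names no response variable. Both the gate and the ANOVA are framed on scores at each visit, so the weak reading is a natural one.

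A reader might also infer that the three visits would be pooled as independent values, with inflated false positives. No text describes that, and it forms no part of this point.

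It can also be said that the gate's failure rate is unknown, and that it depends on whether the test is run on all scores, by cell or on change. For uniform scores tested within one arm of 15, rejection falls to about 13% per test. Within a cell, scores differ from cell-mean residuals only by a constant, so a by-cell check would be a residual check. That limits any claim about how likely the branch is. Nor is the analysis undefined: an objective rule and both branches are prespecified.

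Finally, this is a self-described exploratory pilot reported in a condensed article, and the choice of response variable could sit in a fuller document. That tempers the weight. It does not remove the point, because the gate and the replacement are stated as a rule.

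**Conclusion.** The concern holds in a conditional form. The Kruskal–Wallis fallback is not equivalent to the repeated-measures ANOVA it replaces, and its response variable and visit are not fixed. On raw post-tDCS scores it ignores baseline, and power is about 15% against about 80% for a baseline-adjusted omnibus test. On change from baseline, power is about 75% to 77% and the loss is small, but only one visit pair is tested at a time.

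These figures rest on the assumed baseline spread, change SD and effect. Under other assumptions the gap varies, and it is narrow where visits correlate weakly and spread is large: with clipped scores at SD 20 and correlation 0.80, about 12% for the interaction test against about 10% for the raw rank test. The chance of reaching the branch cannot be pinned down from the article; about 10% to 99% is compatible with the shapes tried. The point concerns the primary outcome and costs little to correct, so it should be settled before the group codes are broken.

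**What to change.** Delete the Shapiro–Wilk gate and the Kruskal–Wallis replacement. Name one primary analysis of FMA-UE that applies whatever the score distribution: a longitudinal mixed model or cLDA on W0, W3 and W7, with baseline-adjusted group contrasts and the Bonferroni correction already stated. For cLDA this is a real change of role, from handling missing data to making the treatment comparison, and the text should say so. Check the model's residuals rather than the raw scores.

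If a rank method is kept, make it a sensitivity analysis. Apply it to change from baseline at a named visit, or use rank ANCOVA with baseline as covariate.

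The cost is a rewording of the Statistical analyses section and a documented change of primary model. It needs no new data, visits or patients.
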